### Outcome measures

The primary outcome and its definition are described in detail below. Pre-specified secondary outcomes are presented in Table 2 below, each with its definition, instrument or data source, timing of ascertainment, and analytic role.

**Table 2 pone.0356813.t002:** Pre-specified primary and secondary outcomes.

Outcome	Definition	Instrument / Data Source	Timing of Ascertainment	Priority	Analytic Role
**Time to fecal continence**	First clinic visit (confirmed at subsequent visit) at which the participant meets social continence threshold: BCS criteria (ARM) or BFS ≥ 17 (HD), from date of definitive repair	BCS (ARM) [16] or BFS (HD) [17], parent/caregiver proxy to age 11; self-report from age 12	Annual visits from age 3	**PRIMARY**	Kaplan–Meier estimation; Cox proportional hazards regression; Fine-Gray model for competing risks; landmark analyses at ages 5 and 10
HD-associated enterocolitis (HAEC)	≥1 physician-confirmed episode meeting Ruttenstock criteria requiring medical treatment	Clinical record review; REDCap adverse event log	Each annual visit; first episode date recorded	Secondary 1	Cox regression / Fine-Gray competing risks; descriptive incidence rate
Reoperation rate	Any unplanned surgical return to the operating room following index repair	Operative report review; REDCap surgical procedure log	Cumulative from index repair; each annual visit	Secondary 2	Cox regression / Fine-Gray competing risks; cumulative incidence curve
Disease-specific quality of life	HAQL total score and subscale scores (age-appropriate version)	HAQL questionnaire, self- or proxy-report [18]	Ages 6, 10, and 14 years	Secondary 3	Linear mixed-effects model (repeated measures); descriptive means by group
Transition readiness	Transition Readiness Assessment Questionnaire	TRAQ [19], self-report	Ages 14 and 17 years	Secondary 4	Linear mixed-effects model; descriptive score trajectory
Loss to follow-up (LTFU)	No clinic encounter, survey, or successful contact for ≥18 months while under age 18 and not yet transitioned	REDCap contact log; clinic attendance record	Flagged at 18-month mark; reviewed at each annual analysis	Secondary 5	Logistic regression (ever-lost vs retained); descriptive LTFU rate

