The primary outcome is time to achievement of fecal continence from the date of definitive surgical repair, analysed as a time-to-event outcome. For participants with ARM, continence is assessed using the Baylor Continence Scale (BCS) [16], with social continence defined as no soiling episodes in the preceding 4 weeks per published BCS criteria, completed by the parent or caregiver proxy up to age 11 and by self-report from age 12. For participants with HD, continence is assessed using the Bowel Function Score (BFS) [17], with social continence defined as a BFS score ≥ 17, administered to the parent or caregiver proxy up to age 11 and by self-report from age 12. Both instruments are administered at every annual clinic visit beginning at age 3 years. The earliest clinically meaningful assessment for continence is age 3, consistent with normal developmental milestones for voluntary bowel control. Participants will be censored at age 18, death, transition to adult care, or loss to follow-up, whichever occurs first.

Pre-specified secondary outcomes, listed in priority order, are: (1) Hirschsprung-associated enterocolitis (HAEC), defined as at least one physician-confirmed episode meeting the Ruttenstock diagnostic criteria and requiring medical treatment, assessed at each annual visit [20]; (2) reoperation rate, defined as any unplanned surgical return to the operating room following index repair, assessed cumulatively; (3) disease-specific quality of life, measured using the HAQL [18] at ages 6, 10, and 14 years using age-appropriate versions; (4) transition readiness, assessed at ages 14 and 17 years using the validated Transition Readiness Assessment Questionnaire (TRAQ) [19], and (5) loss to follow-up rate, defined operationally in the Loss to Follow-Up section. Each secondary outcome will be reported descriptively and, where the events-per-variable threshold is met (see Sample Size section), included as an endpoint in pre-specified multivariable analyses with the analytic role specified in the Statistical Analysis section.

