### Sample size and expected enrolment

The registry is designed for indefinite, continuous enrollment. We distinguish two enrollment streams: incident cases (children newly diagnosed with HD or ARM presenting to COCOE, estimated at a minimum of 5 per month) and previous cases (patients previously diagnosed but lost to follow-up and re-engaged, estimated at approximately 3 per month). Combined, the registry aims to enroll approximately 96 participants per year. Based on a prevalent backlog of an estimated 150–200 patients currently followed at COCOE, total enrollment over 5 years is projected at 480–680 participants.

While no minimum sample size is required for registry operation, we provide a feasibility projection. Based on published ARM cohort data reporting approximately 24–30% achieving full fecal continence [14], and HD cohort data reporting approximately 39% achieving a BFS ≥ 17 by adolescence, we project a combined continence event rate of approximately 30–35% within the first 5 years of registry operation [21]. This corresponds to approximately 145–240 continence events across the projected 480–680 enrolees, supporting inclusion of up to 14–24 covariates in the primary Cox model at an events-per-variable (EPV) threshold of 10 [22]. Importantly, this time-to-event framing includes all enrolled participants regardless of age at enrollment, resolving the limitation of the age-5 cross-sectional design by allowing older prevalent cases to contribute person-time and events from their enrolment date. Pre-specified multivariable analyses will be triggered only once this EPV threshold is confirmed at interim review; otherwise analyses will be limited to descriptive and unadjusted comparisons.

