### Patient-reported outcomes

During clinic visits or between encounters (online or paper), families are asked to complete validated surveys addressing multiple domains of well-being (Table 3). Surveys are available in English and French. Instruments include the Hirschsprung's and Anorectal Malformation Quality of Life (HAQL) questionnaire (disease-specific symptoms and quality of life, with age-specific and stoma-specific versions) [18]; the Baylor Continence Scale (BCS) [16], evaluating the social and functional impact of continence issues; the PedsQL General Well-being Scale [36]; the PedsQL Family Impact Module [36]; the Parent Experience of Child Illness (PECI) [37]; and, for those in bowel management programmes, the Patient-Reported Experience and Outcome Measures in Bowel Management Programmes (PREOM-BMP) [38]. Both French and English validated versions are available and will be used according to family language preference. Proxy-report by the parent or caregiver will be used for children aged 6–11 years; self-report will be used from age 12 onward, consistent with the validated age thresholds for each version.

**Table 3 pone.0356813.t003:** Summary of patient-reported outcome surveys.

Domain	Scale	Duration	Respondent	Brief description
Disease-specific	HAQL and BFS	10–20 min	Child (older) or Parent	Multiple-choice questions about symptoms and QoL; age-specific versions; stoma-specific items.
Social impact	BCS	10–15 min	Child (older) or Parent	23 questions on social continence and impact on life; self- or proxy-report.
General well-being	PedsQL General Well-being	4–10 min	Child or Parent (proxy)	Flexible item banks and short forms assessing physical, mental, and social health; domains include pain, fatigue, physical function, depression, anxiety, and social function.
Family functioning	PedsQL FIM	10–15 min	Parent	36-item parent-report scale assessing physical, emotional, social, and cognitive functioning, communication, worry, daily activities, and family relationships.
Parental well-being	PECI	10–15 min	Parent	25-item measure of adjustment to caring for a child with chronic illness; covers guilt/worry, unresolved sorrow/anger, long-term uncertainty, and emotional resources.
Family experience	PREOM-BMP	10–15 min	Parent	33-item survey for families of children in bowel management programmes; covers physical/emotional health, QoL, treatment success, financial considerations, schooling, and social concerns.

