### Survey administration and burden mitigation

The six instruments have a combined estimated completion time of 54–95 minutes depending on age and programme status. To reduce burden, instruments are administered in a staggered fashion across visits: the HAQL, BCS and BFS are prioritised at each visit; the PedsQL modules and PECI are administered at alternating annual visits; and the PREOM-BMP is administered only to eligible families. Where possible, surveys are distributed electronically via REDCap prior to the clinic visit to allow completion at home, reducing in-clinic time. Paper versions are available for families without internet access, and a trained research assistant is available to assist with completion where literacy or language is a barrier. Surveys are available in English and French. In the event of partial completion, available items will be scored according to the instrument's published scoring guidelines; instruments with fewer than the minimum required items completed will be recorded as missing and addressed per the missing data plan in the Statistical Analysis section. Based on experience from comparable paediatric surgical registries, we anticipate an instrument completion rate of approximately 70–80% per visit; completion rates will be reported at each annual analysis.

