Combining HD and ARM within a single registry carries both operational and analytic risks. Operationally, the two cohorts share only part of the data model. Shared elements (demographics, social determinants of health, health service utilisation, PedsQL modules, PECI, PREOM-BMP, TRAQ, and the loss-to-follow-up definition) are captured on common forms, while disease-specific elements (Krickenbeck classification and the BCS for ARM; length of aganglionosis, HAEC ascertainment, and the BFS for HD) are captured on separate branching instruments, so that no clinician or abstractor is presented with a field that does not apply to the patient in front of them. Analytically, the two cohorts are never pooled for primary, survival, or multivariable analysis, and the events-per-variable threshold is assessed within each cohort separately. This is a conservative choice that may delay adjusted analyses in the smaller HD cohort. Pooling is confined to descriptive summaries of registry-level metrics such as enrollment, data completeness, and loss to follow-up, where disease group will always be reported as a stratifying variable. The main residual risk is therefore loss of statistical efficiency rather than confounding, and it is accepted in preference to a single combined model whose coefficients would be difficult to interpret clinically.

Finally, the primary outcome relies on instruments administered by proxy in younger children and by self-report from age 12, so the change of respondent within an individual’s follow-up may introduce measurement discontinuity. Respondent type will be included as a covariate in longitudinal models, and the pre-specified landmark estimates at ages 5 and 10 fall wholly within the proxy-report period, allowing an interpretation that is unaffected by the transition to self-report.

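### HAQL timing is stated in two ways, and on the 6/10/14 schedule a respondent covariate cannot separate the switch to self-report from the age-10 to age-14 change unless age is assumed linear

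*Protocol article*

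**What the plan says.** **Timing.** In Outcome measures, the Table 2 row for disease-specific quality of life gives "Ages 6, 10, and 14 years", and the text repeats that it is "measured using the HAQL [18] at ages 6, 10, and 14 years using age-appropriate versions". Survey administration and burden mitigation says instead that "the HAQL, BCS and BFS are prioritised at each visit".

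**Respondent.** Patient-reported outcomes states: "Proxy-report by the parent or caregiver will be used for children aged 6–11 years; self-report will be used from age 12 onward".

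**Analysis.** Table 2 gives the analytic role as "Linear mixed-effects model (repeated measures); descriptive means by group". Statistical analysis (Objective 2) applies mixed models to patient-reported scores gathered over several visits.

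**Change of respondent.** The last paragraph of Strengths and limitations acknowledges, for the primary outcome, that switching respondent may break the continuity of measurement. It offers two safeguards: "Respondent type will be included as a covariate in longitudinal models", and continence landmarks at ages 5 and 10, both inside the proxy period.

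**The concern.** If the HAQL is analysed at the three listed ages, the respondent is fully determined by the assessment age: proxy, proxy, self. A model then has nothing with which to tell a child's change between 10 and 14 from the change in who answers. If parents and children systematically score differently, that gap would be read as quality of life improving or worsening on entry to adolescence. The landmark safeguard concerns continence and does not help here.

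The four-year spacing also means that few children could contribute two scores by the Year 4 and 5 report, so early estimates would rest mostly on different children at different ages. Which schedule is meant therefore matters, and the protocol gives two.

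**Working it through.** **1. The plan's enrolment figure.** Incident cases are "estimated at a minimum of 5 per month" and previous cases "estimated at approximately 3 per month". (5 + 3) × 12 = 96 per year, and 96 × 5 = 480. Adding the stated backlog of 150–200 gives 630–680. The printed range of 480–680 therefore runs from no backlog to full backlog. I use 630–680, because most children with repeated scores come from the backlog. The protocol gives no expected number of repeated HAQL scores.

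**2. Can the respondent effect be estimated at 6/10/14?** Let S = 1 for self-report (age 12 or over), and let m6, m10, m14 be the mean scores.
- Categorical age: intercept, age 10, age 14 and S make 4 columns of rank 3. S is the age-14 column.
- Quadratic age: 4 columns, but only three distinct ages, so rank 3.
- Linear age: 3 columns, rank 3. The proxy line extended to 14 is m10 + (m10 − m6), so the S coefficient is m14 − 2·m10 + m6. Three means are fitted with three parameters, so linearity cannot be tested and any curvature goes into S.

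**3. Size of the contamination.** If self minus proxy is d, then m14 − m10 = true change + d, so d enters in full. The documents give no d. As an illustration only, d = 0.3 SD with no true change shows as a 0.3 SD change.

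**4. Children with two scores by year 5 at 6/10/14.** Assumptions (the protocol gives no age distribution): backlog and previous cases uniform over 18 years of age, incident cases enrolled in infancy (no pairs), no loss to follow-up. With f years of follow-up, the share giving a pair is:
- exact birthday: 2(f − 4)/18 for f ≥ 4;
- annual visits counted from enrolment: 2/18 for f from 4 to below 5, and 4/18 at f = 5;
- any time in the year of age: 2(f − 3)/18 for f > 3.

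Previous cases (180 over 5 years): exact 180/90 = 2.0; annual 180/45 = 4.0; any time 36 × 4/18 = 8.0.

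| Backlog pace | Low (150, exact) | High (200, annual) |
|---|---|---|
| All at opening | 150 × 2/18 + 2.0 = 18.7 | 200 × 4/18 + 4.0 = 48.4 |
| Spread over year 1 | 150 × 1/18 + 2.0 = 10.3 | 200 × 2/18 + 4.0 = 26.2 |
| 25% in year 1, rest in years 2–4 | 150 × 0.25/18 + 2.0 = 4.1 | 200 × 0.5/18 + 4.0 = 9.6 |

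The widest rule, with all backlog at opening, gives 200 × 4/18 + 8.0 = 52.4. The range is thus about 4 to 52, or 0.6% of 630 to 7.7% of 680, and about half are 10-and-14 pairs. With the plan's 70–80% completion per visit, taken as independent, 0.49 to 0.64 of pairs remain: about 2 (4.1 × 0.49) to 34 (52.4 × 0.64). All three scores need more than 7 years even on the widest rule, so no child has them by year 5.

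**5. The every-visit reading.** With annual HAQL from 6 to 17, S is estimable with linear age (rank 3 of 3) or quadratic age (4 of 4), but still aliased with categorical age (12 of 13). Simulating annual visits under the same age assumptions gives about 204–267 children with at least two scores (32–39%), of whom about 41–76 have both proxy and self-report scores.

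**The case against.** The strongest reply is that the protocol already plans the HAQL at every visit, and that Objective 2 of Statistical analysis models patient-reported data from several visits. On that reading repeated scores are not few, and a respondent effect can be estimated under a smooth age trend. This stands, and it limits the point. A reader might infer that the HAQL is firmly fixed at three ages, or that Table 2 throws the other scores away. The documents say neither; they leave two schedules unreconciled.

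Second, the respondent covariate is introduced in a paragraph about the primary outcome, and no sentence claims that it solves the problem for HAQL. That also stands. Yet the wording covers longitudinal models in general, the primary outcome is analysed as time to event, and its listed Cox predictors contain no respondent term. A reader would naturally apply the sentence to the HAQL mixed model.

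Third, one might infer that the protocol's patient-reported objective cannot be met. That goes too far. The 6-to-10 contrast is proxy throughout, and Table 3 has the Family Impact Module, PECI and PREOM-BMP answered by parents only.

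Fourth, few pairs at year 5 is not a mistake in an open-ended registry that sets no minimum sample size and uses models that keep incomplete series. Agreed.

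Fifth, annual HAQL does not remove the step at age 12. Agreed: any estimate of that step still leans on an assumed smooth age trend and on the few children who cross it.

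**Conclusion.** The point holds in a limited form. The HAQL schedule is stated in two incompatible ways. If ages 6, 10 and 14 stand, the planned respondent covariate cannot separate respondent from the 10-to-14 change, except under a linear age trend that three ages cannot check, and any systematic proxy–self difference goes into that contrast in full. This follows from the protocol's own ages and respondent rule and needs no outside figure. The size of the proxy–self difference is unknown.

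The count of 4 to 52 children with two scores depends on assumed uniform ages, the visit window and the backlog pace. It falls further with incomplete response, and again if split between ARM and HD. It bears on early precision only.

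The issue affects one contrast of the third-ranked secondary outcome. It should be corrected before the HAQL is analysed; it does not touch the primary outcome.

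**What to change.** - In Table 2 and the Outcome measures text, state that the HAQL collected at each visit enters the mixed model, with ages 6, 10 and 14 as reporting points. This removes the conflict with Survey administration and burden mitigation.
- Estimate trajectories separately within the proxy period (6–11) and the self-report period (12–17).
- State that a difference between ages 10 and 14 will not be interpreted as change in quality of life.
- In Strengths and limitations, add that for HAQL a respondent covariate does not identify the respondent shift, because respondent type is determined by age.

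The cost is a few sentences and a small change to the model specification. No extra questionnaire is needed, since the HAQL is already prioritised at each visit. The price is that there will be no adjusted estimate of change across age 12.

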## Knowledge mobilisation and dissemination

This study uses an integrated Knowledge Translation (iKT) framework, with full inclusion of youth and parent research partners as key knowledge users [45]. Patient partners will review project aims and objectives, co-interpret results, continuously disseminate findings within patient and social networks, and plan further studies. Broader dissemination will occur locally through departmental presentations and nationally through CanCORPS (Canadian Consortium for Research in Pediatric Surgery), the Maternal Infant Child and Youth Research Network (MICYRN), the Alberta Surgery Strategic Clinical Network, and national professional associations. Results will be presented at international conferences and published in a minimum of two peer-reviewed manuscripts. Individual participants will not be identifiable in any publications.

## Protocol registration

This protocol has been registered with ClinicalTrials.gov. Registration number: NCT07603232. Date of registration: 2026-05-22.

## Data sharing statement

De-identified, aggregate data supporting findings from studies conducted using the COCOE Registry will be made available upon reasonable written request to the corresponding author (HW), subject to ethics approval from the requesting institution and execution of a data sharing agreement with the RI-MUHC. Individual-level participant data will not be shared publicly given the privacy obligations arising from the registry's consent framework and applicable Québec privacy legislation (Law 25). No data are available at the time of protocol publication.

As the registry has no fixed completion date, data sharing operates continuously rather than at a single terminal point. Specifically: (i) the full data dictionary, REDCap instrument definitions, and analysis code will be deposited in a public repository (Open Science Framework) at the time of first results publication and will carry a citable digital object identifier; (ii) the de-identified aggregate data underlying every figure and table in each registry publication will be provided as supporting information with that publication, in accordance with PLOS data policy; (iii) requests for de-identified individual-level data will be reviewed by a standing data access committee chaired by the registry Director against pre-specified criteria (scientific merit, ethics approval at the requesting institution, and an executed RI-MUHC data transfer agreement), with a target decision within 60 days and a publicly maintained log of approved requests; and (iv) should the registry cease operation, the de-identified dataset and its documentation will be transferred to a controlled-access repository under RI-MUHC custodianship so that it remains available for secondary research.

Individual-level data cannot be placed in an unrestricted public repository because the consent obtained from participants and the requirements of Québec Law 25 do not permit unrestricted redistribution of a longitudinal dataset of children with rare congenital conditions, for whom the combination of diagnosis, severity category, syndromic status, and follow-up dates carries a residual risk of re-identification. Requests may be directed to the corresponding author or to the RI-MUHC Research Ethics Office.
